## Discussion

This is the first study that we are aware of that will use adaptive trial methodology in the context of randomising clusters rather than individuals. In this paper, we describe the methodological approaches to developing an adaptive CRT, to provide timely and cost-efficient understanding of optimal strategies to improve uptake of HIV testing and linkage into HIV care and prevention among male partners of pregnant women in a high HIV-prevalent setting. The methodology and lessons learned here will be important as proof of concept of how to design and conduct similar studies in the future. Being a phase II trial means that fewer resources can be allocated to a “learning” phase of a major phase III trial to narrow down to interventions that hold true rather than assumed potential effectiveness. As a multi-arm trial it allows the investigation of interventions that can act on their own, such as providing self-test kits only, or in combination, where an incentive or a reminder is given. This approach, which is one of the key strengths of adaptive trials, allows generation of clear evidence relating to specific intervention components that are effective when compared to the SOC.

The 2020 UNAIDS targets set in 2014 aim to diagnose 90% of people living with HIV and to start 90% of those diagnosed on ART, leading to virus suppression in 90% of those on ART [5]. While HIVST has been shown to increase uptake of HIV testing to within the first 90%, very limited evidence exists on effective interventions for improving linkage into care, the second 90%. In a recent trial in rural South Africa and Uganda, having a lay counsellor visit newly diagnosed individuals had minimal impact on linkage (risk ratio of 1.04) [38]. A combination strategy of conducting point-of-care CD4 at the time; accelerated ART initiation for adults with CD4 < 350 cells/uL; mobile phone appointment reminders; health educational packages; and non-cash financial incentives improved from 83% in the SOC arm to 92% in CRT in Swaziland [39]. However, the authors acknowledged that the multiplicity of interventions offered in the trial obscure the isolation of successful intervention components. Therefore, though small, this trial will potentially present good evidence on the type of effective interventions for improving linkage to HIV care or prevention, and also the right dose for financial incentives that may be effective.

The trial results will also have important policy implications on how to implement HIVST targeting male partners of pregnant women who are accessing ANC for the first time while paying particular attention to safety concerns. In a recent cohort study where HIV-negative pregnant women collected three oral self-test kits in Kenya 51% reported that their male partners had self-tested with none of the women reporting any SAEs [40]. Unlike in the Kenya study, where only HIV-negative pregnant women were eligible, this trial will recruit pregnant women, regardless of HIV status, who are attending their first ANC. The group of women recruited here receive the offer of an HIV test routinely making this trial design readily scalable. Measuring actual HIV testing is extremely difficult with HIVST as by definition disclosure depends on the individual. Our HIV testing outcome will be measured objectively through observed returned used/unused self-test kits by the man and also proxy reporting by the woman which minimises information bias.

A major anticipated constraint is potential for SAEs resulting mainly from intimate partner violence (IPV) to women, although evidence from studies using other populations and other HTS models suggests that this approach is unlikely to increase this problem [6]. A recent large HIV self-testing study in Malawi found no increase in IPV, despite an active community liaison system among 27,000 self-testing participants [20]. We will carefully monitor IPV, and have deliberately listed this as a secondary (safety) outcome. Although it will not be possible for participants and recruiting staff to predict the next-day recruiting arm, the knowledge of FI arms may result in altered decision-making about health care seeking. For example, a woman may choose to postpone her ANC attendance in the hope of being recruited in a FI arm, or indeed want to switch between arms.

There is potential for contamination if women in the intervention arms share their self-test kits with women in the SOC arm. In order to minimise this problem, we will ask women and their male partners in the intervention arms to bring used or unused self-test kits at follow-up and when they link into the MFC, respectively. We will also attempt to measure the magnitude of this problem by asking all women and male partners who link into the MFC in the SOC arm if they received self-test kits. There is potential bias in the estimation of the treatment effect and confidence intervals due to interim selection process of potential effective interventions which we will not explore.

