### Sample size considerations

A modification of the formula for sample size calculation for a MAMS design for binary outcomes [32] was made based on the methodology for CRTs [33] to identify each stage of the trial. We assume that each ANC day will have at least 40 women attending for the first time, 90% will satisfy the eligibility criteria and at least 60% will consent to participate, so having a cluster size of at least 21. We also assume that in the SOC arm 25% of men will satisfy the definition of the primary outcome [34]. For the first stage, six ANC days per arm (36 days in total) would be needed to detect an absolute difference of 15% in linkage compared to 25% in the SOC arm using a FWER of 0.2 with 80% pair-wise power and a coefficient of variation (*k*) of 0.10 [21]. In general, under the stated assumptions the trial has 80% chance of detecting a 1.6-fold increase in testing and linkage within 28 days compared to SOC at 5% significance level. Sample size for the second stage will be re-calculated based on empirical estimates at interim analysis with FWER of 0.1 and 80% power.

Very little clustering within ANC days is expected, hence we have assumed that *k* = 0.10 (intraclass correlation coefficient = 0.003). The simulation study assumed that *k* = 0.2 and differs with the final design in this respect resulting in six and seven clusters per arm in the final design and the simulation, respectively. A larger than conventional (0.05) FWER of 0.2 and 0.1 for stage 1 and stage 2, respectively, may lead to erroneously taking forward an ineffective intervention. However, given that this is a phase II trial this is not a major concern as it guards against dropping interventions that may otherwise prove to be effective in a larger, phase III trial. A more conventional pair-wise power of 0.8 was chosen to ensure that there is a high chance of taking forward most of the efficacious interventions from stage 1.

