### Statistical analysis

Analyses will be done in R [35] and Stata 14.0 (Stata Corp., TX, USA). Baseline characteristics will be computed as proportions or median (interquartile range (IQR)), as appropriate, by arm in each of the two stages of the trial. Any variables that show imbalances will be adjusted [33] for when analysing the trial outcomes at the end of the second stage. We will assume that the two stages of the trial are independent [26] and will proceed to carry out a test of the null hypothesis of no difference in effectiveness of each intervention compared to the SOC. We will do this by analysing data from the first stage first followed by interim decisions to drop arms; then we will conduct and analyse data from the second stage (no overlap of participants from the first stage). Analysis of the whole trial will then be based on combined *p* values from both the first stage and the second stage using the weighted inverse normal (WIN) method [36] for arms that are not dropped at interim. A weighted average of the log (risk ratio (RR)) will be computed for the whole trial using estimates from each trial stage. All analyses will be by intention-to-treat taking as the denominator the number of women who were eligible and take into account the clustered design.

Given the small number (six) of clusters per arm in the first stage, analysis will be by cluster-level summaries using mean of proportion of male partners per clinic day who link to care or prevention in each arm [33]. The proportion of male partners who link into care or prevention will be computed per clinic day for each arm with number of men achieving the primary outcome and the number of women eligible and recruited in ANC on enrolment day as denominator. A log transformation of the clinic day proportions will be applied if a positive skew is observed [33]. The geometric mean of clinic day proportions in each of the five intervention arms will be compared to the SOC arm using an unpaired *t* test [33]. An estimate of the RR and a 95% CI will also be computed for each comparison by dividing the geometric mean of proportions in each intervention arm and the geometric mean of proportions in the SOC arm [33].

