## Trial status

At the time of submission on 9 November 2016, 32 of 36 clusters (total of 800 participants recruited) were covered for the first of the two trial stages. Interim analysis is planned for 20 January 2017. The second stage is planned to run for 4 months; we will compute the required sample size for the second stage at interim analysis to achieve the specified 80% power.

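### The whole-trial risk ratio averages in the stage-1 result that selected the arm; the plan admits the bias and declines to examine it, and does not say which interim estimates will re-size stage 2

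*Protocol article*

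**What the plan says.** - **Selection.** Under Design and Adaptations at interim analysis, an intervention arm with p > 0.2 against standard of care (SOC) is considered for dropping, alongside safety and cost. Statistical analysis says the p value used is Dunnett-corrected. There is no early stop for efficacy.
- **Final estimate.** Statistical analysis tests retained arms by combining stage-wise p values with the weighted inverse normal (WIN) method. A weighted average of the log RR "will be computed for the whole trial using estimates from each trial stage". The weights are not given. Stage-2 participants do not overlap with stage 1.
- **Acknowledged bias.** The Discussion notes possible bias in the treatment effect and its confidence interval "due to interim selection process of potential effective interventions which we will not explore".
- **Re-sizing.** Sample size considerations: "Sample size for the second stage will be re-calculated based on empirical estimates at interim analysis with FWER of 0.1 and 80% power". Trial status repeats the aim: "we will compute the required sample size for the second stage at interim analysis to achieve the specified 80% power". Neither place says whether the estimates include the retained arms' observed effects or only nuisance values (SOC proportion, k, cluster size).

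**The concern.** An arm that continues because its stage-1 result was favourable carries, on average, a stage-1 RR that is too high. Averaging that RR with an unbiased stage-2 RR halves the bias on the log scale under equal weights but does not remove it, and the interval is centred on the biased value. The WIN combination addresses the test. It does nothing for the estimate.

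This is a stated decision rather than a detail left to the analysis plan: the article names the bias and rules out looking at it. The trial is meant to pick candidates for a phase III trial, so a reader would naturally take the whole-trial RR into phase III planning. If the inflated stage-1 effect also sets the stage-2 size, stage 2 would be smaller than its stated power requires.

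**Working it through.** **Inputs.** From Sample size considerations: "six ANC days per arm (36 days in total) would be needed to detect an absolute difference of 15% in linkage compared to 25"% in SOC, "using a FWER of 0.2 with 80% pair-wise power"; 40 × 0.90 × 0.60 = 21.6 women per day, "so having a cluster size of at least 21"; and "we have assumed that *k* = 0.10 (intraclass correlation coefficient = 0.003"). From Tables 1 and 2: true proportions 0.25 (SOC) and 0.29, 0.30, 0.31, 0.32, 0.40. Assumed because the article does not state them: equal stage weights, retention only of arms better than SOC with p ≤ 0.2, two-sided tests, and arithmetic means of cluster proportions.

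**1. The plan's own figure.** Cluster formula: c = 1 + (z_α + z_β)² V / d², with V = p0(1−p0)/m + p1(1−p1)/m + k²(p0² + p1²).
- V = 0.008929 + 0.011429 + 0.002225 = 0.022583; d² = 0.0225.
- With z_α = 1.282 (unadjusted two-sided 0.2) and z_β = 0.842, c = 5.52, so 6 days per arm. With k = 0.2 it gives 6.86, so 7.
- Both match the article. The match needs the unadjusted level, which is a separate matter and is not relied on here.

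**2. Stage-1 RR given retention.** Simulated first stages: beta-binomial clusters, 6 days per arm, m = 21, k = 0.10, unpaired t tests, Dunnett p ≤ 0.2.
- True 0.40 (RR 1.60): retained about 64% of the time; mean difference 0.183 against 0.150; RR 1.79.
- True 0.29–0.32 (RR 1.16–1.28): retained 11–22% of the time; RR 1.64–1.67.
- True null: retained about 3%; RR about 1.62.

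**3. Pooled RR, equal weights.** The stage-2 data are not selected on, so their RR averages the truth. On the log scale the pooled value is the geometric mean of the two.
- √(1.79 × 1.60) = 1.69 against 1.60, about 6% too high.
- √(1.64 × 1.16) = 1.38 against 1.16, and √(1.67 × 1.28) = 1.46 against 1.28: 19% and 14% too high.
- Null: √(1.62 × 1.00) = 1.27.

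**4. Sensitivity.**
- Uncorrected p ≤ 0.2: stage-1 RRs are 1.51–1.54 for the weak arms and 1.69 for the 0.40 arm. Pooled: √(1.51 × 1.16) = 1.32, √(1.54 × 1.28) = 1.40, and about 1.65 for the 0.40 arm.
- Dunnett rule with two thirds of the weight on stage 2: 1.79^(1/3) × 1.60^(2/3) = 1.66; 1.64^(1/3) × 1.16^(2/3) = 1.30; 1.67^(1/3) × 1.28^(2/3) = 1.40. The bias is smaller but still present.

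**5. Stage-2 size.** Take two retained arms and FWER 0.1, so the Dunnett critical value is 1.918, and (1.918 + 0.842)² = 7.62.
- Design difference 0.15: c = 1 + 7.62 × 0.022583/0.0225 = 8.6, so 9 days. Power at the true difference is Φ(√(8 × 0.0225/0.022583) − 1.918) = Φ(0.905) = 0.82.
- Mean retained difference 0.183 (V held as above): c = 1 + 7.62 × 0.022583/0.0335 = 6.1, so 7 days. Power at the true 0.15 is Φ(√(6 × 0.0225/0.022583) − 1.918) = Φ(0.527) = 0.70.
- Simulating the whole re-sizing step gives about 0.69–0.75 for a true 0.40 arm sized on its own observed effect, 0.83 (0.76–0.94 across scenarios) on the smallest retained effect, and 0.80–0.82 on the fixed 0.15 difference.

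**The case against.** Several points on the other side stand.

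- **The drop rule is not binding.** An arm with p > 0.2 is only considered for dropping and may be kept on cost grounds. If such arms are kept, selection is weaker and the bias smaller than modelled.
- **The weights are unstated.** A larger weight on stage 2 reduces the bias, as step 4 shows.
- **A stage-2 RR will probably exist anyway.** Stage 2 is analysed in the same way as stage 1, and the pooled RR needs both stage estimates. The article does not, however, say that the stage-2 RR will be reported or what it is for.
- **Nothing says phase III will be sized on the pooled RR,** and the article knowingly accepts carrying some ineffective arms forward at phase II. That tolerance concerns the error rate. It does not justify a biased estimate.

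A reader might go further and infer that stage 2 will miss its 80% power. The documents do not support that: the wording on interim estimates fits updating nuisance values alone, which gives about 0.80–0.82. Nor is low stage-2 power for arms at 29–32% evidence of harm from re-sizing. The 80% target is set for a 0.15 difference, and 9 days per arm at the design difference would give those arms only about 13–29%.

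A shortfall in stage 2 would also not be a whole-trial shortfall. The final decision uses the WIN p value, and a retained 40% arm is rejected about 98–99% of the time (equal weights and a 0.1 level assumed).

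**Conclusion.** The point holds for estimation. The whole-trial RR includes the result on which the arm was selected, and the plan acknowledges the bias but declines to examine it. Under the Dunnett rule applied strictly, with equal weights, k = 0.10 and m = 21, retained weak arms show a pooled RR of about 1.38–1.46 for a true 1.16–1.28, and a retained arm at the design effect shows about 1.69 for a true 1.60. It would be too strong to say that every retained arm looks far better than it is: the large inflation belongs to weak or null arms that happen to pass, and it is modest at the design effect. The WIN test is not in question.

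The re-sizing point is secondary and conditional. The article leaves the driving estimates open, and power falls short (about 0.69–0.75 for a true 40% arm) if that arm's own observed effect is used.

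**What to change.** 1. Keep the WIN p value and the pooled RR. Beside it, report for each retained arm the stage-2-only RR and 95% CI, or a conditionally bias-adjusted RR.
2. State that selection biases the pooled RR away from 1, and that the stage-2 or adjusted RR should inform phase III planning. Making the stage-2 RR the sole headline would be a trade-off between bias and precision and is not needed.
3. Delete the closing clause of the Discussion sentence that declines to explore the bias.
4. In Sample size considerations, limit the stage-2 re-calculation to the SOC proportion, k and cluster size, and keep the 0.15 design difference.

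Items 1–3 need no new data; the cost is a wider interval on the additional estimate. Item 4 costs about 9 days per arm with two arms retained, against a median of 7–8 if the observed difference were used.

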## Trial status

At the time of submission on 9 November 2016, 32 of 36 clusters (total of 800 participants recruited) were covered for the first of the two trial stages. Interim analysis is planned for 20 January 2017. The second stage is planned to run for 4 months; we will compute the required sample size for the second stage at interim analysis to achieve the specified 80% power.

## Abbreviations

ACASI: Audio computer-assisted self-interview
ANC: Antenatal clinic
ART: Antiretroviral treatment
CI: Confidence interval
COMREC: College of Medicine Research and Ethics Committee
CRT: Cluster randomised trial
DSMB: Data Safety and Monitoring Board
FI: Financial incentive
FWER: Family wise error rate
HIV: Human immunodeficiency virus
HIVST: HIV self-testing
HTS: HIV-testing services
IQR: Interquartile range
LSHTM: London School of Hygiene and Tropical Medicine
MAMS: Multi-arm multi-stage
MFC: Male-friendly clinic
MLW: Malawi Liverpool Wellcome Trust Clinical Research Programme
PHC: Primary health centre
PITC: Provider-initiated testing and counselling
RR: Risk ratio
SAEs: Serious adverse events
SD: Standard deviation
SMS: Short messaging service
SOC: Standard of care
SSA: Sub-Saharan Africa
VMMC: Voluntary male medical circumcision
WIN: Weighted inverse normal
